## Methods/design

This is a stepped wedge cluster randomised trial for the implementation of an intervention at hospital level to evaluate whether a risk stratification model can reduce the incidence of preterm deliveries among women with suspected or confirmed preeclampsia. The trial will be conducted in seven tertiary centres, geographically dispersed throughout Brazil, and will run for 48 months; with data collection for 32 months. The participating tertiary centres and respective cities are: Fernandes Figueira Institute, Rio de Janeiro; Maternity Maria Amélia Buarque de Holanda, Rio de Janeiro (these two hospitals constitute one centre for the study); Maternity Leila Diniz, Rio de Janeiro; Botucatu Medical School, Botucatu-SP; Center for Women’s Health – CAISM, Campinas-SP; Hospital Guilherme Álvaro, Santos-SP; Maternity Leonor Mendes de Barros, São Paulo; Hospital of Clinics of Porto Alegre-RS.

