### Randomisation, recruitment and collection of baseline data

Randomisation will be undertaken by the trial statistician through a computer-generated blocking list at the start of the trial, but the timing of implementation of the intervention to each centre will be revealed only 30 days before the transition phase.

Recruitment will be performed by responsible doctors at each centre. At the start of the trial period, all women with suspected or diagnosed pre-eclampsia will be managed according to current local protocols. Subsequently, every four months, one centre will enter the transition phase to the implementation of the intervention (Fig. 1). All centres will continue the baseline data collection until randomised to implementation. Once each centre has crossed over to the intervention, it will continue to implement the intervention as part of routine care until the end of the study. After the last centre has crossed over, the trial continues a final four-month period during which all centres will be implementing the intervention. The effectiveness of the intervention will be measured by comparing the aggregated data of the centres in the pre-implementation phase of the trial with those in the post-implementation phase.

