### Statistical issues

#### Sample size

The primary aim is to test whether care targeted at preventing unnecessary delivery of women with pre-eclampsia will reduce the proportion of women delivered in the centres with preterm pre-eclampsia (deliveries with preterm pre-eclampsia/total deliveries). The power calculation depends on estimates of the total number of births, current pre-eclampsia prevalence and proportion with preterm deliveries from the seven centres (which have already agreed to participate). We estimate the mean number of infants born in each month per centre to be 330, and that of these ~ 5% will be born to women with pre-eclampsia. The preterm rate among those women with pre-eclampsia is approximately 36%. Therefore each month, there will be the potential to enter 17 women with pre-eclampsia, of whom approximately 6 would deliver prematurely, and outcome data will be available for approximately 700 deliveries of women with preterm pre-eclampsia. There is limited information on likely intracluster correlation (ICC) for this outcome in this setting and so we have explored sensitivity to a range of values.

Power calculations for stepped wedge cluster trials were as described in Hussy and Hughs [18]. Assuming that seven centres take part and allowing for a one month transition phase, and that in each centre there are approximately 17 cases of pre-eclampsia and 330 deliveries per month (with outcome data available for all deliveries), this study will have 89.6% power to detect a reduction in preterm deliveries associated with pre-eclampsia in the study centres from a population estimate of 1.5 to 1.0%, representing a 33% risk reduction, and 79.6% power to detect a reduction from 2.0 to 1.5% (25% risk reduction). Although the ICC is included in the power calculation, the design was found to be insensitive to the ICC and sensitivity analyses showed that these calculations were robust to larger magnitudes of ICCs.

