### Data analysis

Hospital baseline characteristics of pregnancy outcomes to be collected throughout the data retrieval period will include numbers of women developing pre-eclampsia, women with preterm pre-eclampsia, gestational age at delivery of all hospital deliveries, and maternal and neonatal inpatient nights in women with pre-eclampsia. These baseline characteristics will be compared between exposure and non-exposure to the intervention and will be summarised by their means and standard deviations, medians and inter-quartile ranges, or numbers and percentages as appropriate. Centres will be classified as being exposed to the intervention one month after the centre was randomised to the intervention, and outcomes during the transition months will not be included.

The primary goal of the study is to test whether a care pathway targeted at preventing unnecessary delivery of women with pre-eclampsia will reduce the proportion of women delivered in the centres with preterm pre-eclampsia (deliveries with preterm pre-eclampsia/total deliveries). In statistical terms this null-hypothesis (no difference) can be tested using a mixed effects logistic regression model, with an indicator of whether the centre was exposed to the intervention as the dependent variable. Important independent variables to consider are the clustering effect (i.e. effect of centre), calendar time effect (since the intervention is sequentially rolled-out) and an indicator of intervention exposure for each centre at each time point; in additional to adjustment for other characteristics. Both individual and cluster level covariates to be included in the adjustment will be pre-specified and will include maternal age, parity, pre-existing chronic hypertension or other risk factors for prematurity. Null hypotheses and analyses for secondary outcomes take a similar form to that for the primary outcome, with appropriate link functions in the generalized linear mixed model. Summary treatment effect estimates will be reported (odds ratios or risk ratios) along with 95% CIs. These models will be fitted using population-averaged models using mixed effects methods in Stata version 14.2 or later (StataCorp, College Station, Texas).

The final trial dataset access will be limited to the authors of this study protocol.

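### The claim that power is insensitive to the ICC, and a clustering model with a centre effect alone, hold only if centres do not drift between periods; the estimator sentence also names two different methods

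*Protocol article*

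**What the plan says.** The Sample size section states 89.6% power for a fall from 1.5 to 1.0% and 79.6% for a fall from 2.0 to 1.5%, using the Hussey-Hughes stepped wedge method. It says that little is known about the ICC, gives no value, and concludes that "the design was found to be insensitive to the ICC and sensitivity analyses showed that these calculations were robust to larger magnitudes of ICCs".

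The Data analysis section names a mixed effects logistic regression for the primary test and lists the terms: "Important independent variables to consider are the clustering effect (i.e. effect of centre), calendar time effect", then intervention exposure and covariates. No listed term lets a centre's rate vary from one period to the next. Effects are to be reported with 95% confidence intervals; no alpha is stated. On estimation it says: "These models will be fitted using population-averaged models using mixed effects methods in Stata version 14.2 or later".

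**The concern.** In a stepped wedge trial each centre is largely its own control over time. A centre effect that stays constant cancels from the before-and-after comparison, so a larger ICC of that kind costs almost no power. If part of the centre variance differs by period (case mix, referral patterns, staffing), that part does not cancel. It also does not shrink as deliveries accumulate within a period, and the centre-periods here are large, so it can rival the binomial noise. A model without such a term then gives intervals that are too narrow, and the reassurance about larger ICCs fails at just those ICCs.

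The estimator sentence raises a second problem. A population-averaged model (GEE) estimates a marginal effect, usually with robust standard errors that rely on many clusters. A mixed model estimates an effect conditional on centre, with model-based standard errors. With seven centres the choice changes the false-positive rate, and the sentence names both.

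**Working it through.** **Inputs from the article**
- "Assuming that seven centres take part and allowing for a one month transition phase" (Sample size).
- "every four months, one centre will enter the transition phase to the implementation of the intervention" (Randomisation section), "with data collection for 32 months" (Methods/design): 32/4 = 8 periods, with one centre crossing at each of seven steps.
- Mean of 330 deliveries per centre per month: 4 × 330 = 1,320 per centre-period.
- "outcomes during the transition months will not be included" (Data analysis): 3 × 330 = 990 in the period with the transition month.

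**Assumed, because not stated:** two-sided 5% z test, control-rate variance, ICC ρ and CAC (the share of centre variance that is constant over time).

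**Formulas.** With σ² = p(1−p), the covariance of a centre's period means has off-diagonal elements σ²ρ·CAC and diagonal elements σ²ρ + σ²(1−ρ)/n. With period indicators and exposure in X, SE² is the exposure element of (ΣX′V⁻¹X)⁻¹. Power = Φ(δ/SE − 1.96), with δ = 0.005 in both scenarios.

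**Step 1: reproduce the plan.** With CAC = 1 and ρ = 0.0006:
- 1.5 to 1.0%: SE = 0.001554, 0.005/0.001554 = 3.218, Φ(1.258) = 89.6% (stated 89.6%).
- 2.0 to 1.5%: SE = 0.001789, 0.005/0.001789 = 2.794, Φ(0.834) = 79.8% (stated 79.6%).

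**Step 2: raise the ICC with CAC = 1.** At ρ = 0.01 power is still 86.8% and 76.2%. The insensitivity claim is therefore a true result of the model used.

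**Step 3: let CAC fall below 1.** The last column is the rejection rate of a nominal 5% test on the centre-only model under no effect, at a rate of 1.8%. It equals 2[1 − Φ(1.96/r)], where r is the true SE divided by the model's SE.

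| ICC | CAC | SE, 1.5→1.0% | Power | SE, 2.0→1.5% | Power | Rejection |
|---|---|---|---|---|---|---|
| 0.0006 | 1 | 0.001554 | 89.6% | 0.001789 | 79.8% | 5% |
| 0.0006 | 0.9 | 0.001597 | 88% | 0.001840 | 78% | 6% |
| 0.0006 | 0.8 | 0.001636 | 86% | 0.001884 | 76% | 7% |
| 0.001 | 1 | 0.001583 | 88% | 0.001823 | 78% | 5% |
| 0.001 | 0.9 | 0.001666 | 85% | 0.001918 | 74% | 6% |
| 0.001 | 0.8 | 0.001740 | 82% | 0.002004 | 70% | 8% |
| 0.005 | 1 | 0.001623 | 87% | 0.001869 | 76% | 5% |
| 0.005 | 0.9 | 0.002053 | 68% | 0.002364 | 56% | 12% |
| 0.005 | 0.8 | 0.002395 | 55% | 0.002759 | 44% | 19% |

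As an example, at ICC 0.005 and CAC 0.8, r = 1.489, 1.96/1.489 = 1.316, and the rejection rate is 18.8%.

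**Why the ICC then matters.** For p = 1.5%, σ² = 0.015 × 0.985 = 0.014775. At ICC 0.005 the binomial variance of a centre-period is 0.014775 × 0.995/1,320 = 0.0000111, and the drift variance at CAC 0.8 is 0.014775 × 0.005 × 0.2 = 0.0000148, which is larger. At ICC 0.0006 the drift variance is 0.014775 × 0.0006 × 0.2 = 0.0000018, a small addition.

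**Step 4: simulation check.** In 2,000 null trials per setting, a logistic model with centre effects rejected 5.2-5.6% at CAC = 1. At CAC 0.8 it rejected 7.9% at ICC 0.001 and 20.0% at ICC 0.005. An exchangeable GEE with robust errors and a z reference rejected about 16% at CAC = 1, and 14-20% over all settings.

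**Sensitivity to the variance used.** Averaging the two arms' variances gives higher power. At CAC 0.8, moving from ICC 0.001 to 0.005 takes it from 88% to 63% (1.5 to 1.0%) and from 76% to 49% (2.0 to 1.5%). The pattern is the same.

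**The case against.** Several stronger readings are tempting, and the article does not support them.

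- **That the stated power is wrong.** It is not an arithmetic error: it reproduces within its own model, and so does the flat response to the ICC.
- **That type I error is misstated.** No alpha or type I error is stated. What can be said is that a nominal 5% test and a 95% interval would not hold their level under drift.
- **That neither estimator is valid.** With CAC = 1 the centre-effect model holds 5%. The section also names a mixed model for the primary test and a generalised linear mixed model for secondary outcomes, so the 16% figure belongs to one reading of one unclear sentence and should not set the headline.
- **That no small-sample correction is planned.** The article condenses a fuller plan, and a correction may be in an analysis plan not shown. A normal critical value in the power calculation is likewise inferred. The cost of a t reference depends on its degrees of freedom: at ICC 0.001 and CAC 1, 42 df gives 87.0% and 76.4%, while 5 df gives 71.5% and 59.7%.
- **That the harm is certainly large.** At the ICC implied by the stated power, about 0.0006, it is modest. The worst rows need ICC 0.005, a between-centre coefficient of variation of √(0.018 × 0.982 × 0.005)/0.018 = 52% at a 1.8% rate, as well as drift.

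These points limit the size of the concern. Two things remain: the article declares larger ICCs harmless without the condition that makes this true, and one sentence names two estimators.

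**Conclusion.** **Wrong as written** on two counts: the unconditional claim of robustness to the ICC, and the sentence that combines two different estimators. **Cheap improvement** on two others: a centre-by-period term, and inference suited to seven clusters.

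The size depends on ICC and CAC values that the article does not give. Over the assumed CAC of 0.8-0.9, the loss against the stated power at ICC 0.0006 is about 2 to 4 points in each scenario, and the nominal 5% test is only slightly liberal. At ICC 0.005 power is about 55-68% and 44-56%, and that test rejects a true null in about 12-19% of trials. All these figures use control-rate variance and a two-sided 5% z test. If CAC is 1, both the stated power and the level of the centre-effect model stand.

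**What to change.** 1. Name one estimator: a logistic mixed model with fixed period effects, a random centre effect and a random centre-by-period effect. Remove the population-averaged wording.
2. Base the primary p-value and confidence interval on a method suited to seven clusters. One option is a permutation test over the crossover orders that the actual randomisation scheme allowed. The Randomisation section mentions blocking, so that set should not be taken as all 7! = 5,040 orders without checking. Another option is a centre-period analysis with a t reference. If the analysis plan already contains such a method, refer to it.
3. State that insensitivity to the ICC is conditional on CAC = 1. Report power over a grid of ICC (for example 0.0006-0.005) and CAC (0.8-1.0), giving the variance and reference distribution used.

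The cost is some wording and analysis work, wider intervals and a less favourable stated power. Conduct and data collection do not change. The choice should be fixed before outcomes are analysed.

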## Discussion

Pre-eclampsia is heterogeneous with an unknown number of variants [1, 2]. We believe that there may be pathophysiological differences and other risks specifically relevant to Brazil and perhaps low-income countries in general. Therefore, the PREPARE study will bring the possibility of a better understanding of PE in these settings.

Remarkably, all information available on risk stratification in preeclampsia comes from high-income countries. Few studies have been done in the geographical settings where 99% of maternal mortalities occur. A national survey conducted in Brazil demonstrated a maternal near miss incidence of 10.2 per 1000 live births. Hypertensive disorders comprised the most prevalent complications in this group of patients [8]. Additionally, The Brazilian Network for Surveillance of Severe Maternal Morbidity (SMM), a cross-sectional multicentre study conducted in 27 referral hospitals across the country, classified 10 of these hospitals as providing inadequate care [30].

The surveillance of pre-eclamptic patients developed in PREPARE has the potential to qualify the health care assistance in the centres and if the intervention is implemented appropriately has the potential to reduce PTB and improve care of women with PE without significant adverse side effects. If successful, this novel pathway of care will be presented to health authorities to be adopted as part of a public health policy to help reduce SMM and maternal mortality rates in Brazil. This approach should be transferrable to other low or middle income countries or high-income settings with an excess of premature deliveries for preeclampsia.

## Data Availability

Not applicable.

## Abbreviations

BP: Blood pressure
DMC: Data safety and monitoring committee
fullPIERS: Model for risk stratification in preeclampsia
HELLP: Hemolysis, Elevated Liver, Low Platelets
HIC: High-income countries
KT: Knowledge transfer
PE: Pre-eclampsia
PlGF: Placental growth fator
PREPARE: Prematurity REduction by Pre-eclampsia cARE
PTB: Preterm birth
sFlt-1: Soluble fms-like tyrosine Kinase-1
SMM: Severe Maternal Morbidity
